## Abstract

**Introduction:**

Leprosy, or Hansen’s disease, remains a cause of preventable disability. Early detection, treatment and prevention are key to reducing transmission. Post-exposure prophylaxis with single-dose rifampicin (SDR-PEP) reduces the risk of developing leprosy when administered to screened contacts of patients. This has been adopted in the WHO leprosy guidelines. The PEP4LEP study aims to determine the most effective and feasible method of screening people at risk of developing leprosy and administering chemoprophylaxis to contribute to interrupting transmission.

**Methods and analysis:**

PEP4LEP is a cluster-randomised implementation trial comparing two interventions of integrated skin screening combined with SDR-PEP distribution to contacts of patients with leprosy in Ethiopia, Mozambique and Tanzania. One intervention is community-based, using skin camps to screen approximately 100 community contacts per leprosy patient, and to administer SDR-PEP when eligible. The other intervention is health centre-based, inviting household contacts of leprosy patients to be screened in a local health centre and subsequently receive SDR-PEP when eligible. The mobile health (mHealth) tool SkinApp will support health workers’ capacity in integrated skin screening. The effectiveness of both interventions will be compared by assessing the rate of patients with leprosy detected and case detection delay in months, as well as feasibility in terms of cost-effectiveness and acceptability.

**Ethics and dissemination:**

Ethical approval was obtained from the national ethical committees of Ethiopia (MoSHE), Mozambique (CNBS) and Tanzania (NIMR/MoHCDEC). Study results will be published open access in peer-reviewed journals, providing evidence for the implementation of innovative leprosy screening methods and chemoprophylaxis to policymakers.

**Trial registration number:**

NL7294 (NTR7503).

Strengths and limitations of this studyIn both interventions, a combination of screening contacts and providing post-exposure prophylaxis with single-dose rifampicin will be used according to the WHO’s guidelines to reduce the contacts’ risk of developing leprosy.An integrated skin screening approach will be used in which multiple diseases can be detected and treated at once, overcoming the often negative associations with leprosy.The SkinApp will be used as a mobile health tool to support peripheral health workers in recognising and treating signs and symptoms of skin diseases; while innovative and potentially increasing capacity, the accuracy and reproducibility of this tool awaits further investigation.Since the epidemiological impact on the new case detection rate will not become apparent within the study duration, the primary outcome measures are case detection delay, number of contacts diagnosed with leprosy and number of contacts who received chemoprophylaxis.Because difficulties in recalling the first signs and symptoms are expected to increase over a longer duration of the disease, only recently diagnosed index patients will be included in this study to establish case detection delay.

## Introduction

Leprosy, or Hansen’s disease, is a communicable disease caused by *Mycobacterium leprae* that is still a public health problem in many countries. It is formally recognised by the WHO as a neglected tropical disease (NTD).^1^ The annual reported number of newly detected patients with leprosy was 202 185 in 2019.^2^ If left untreated, leprosy potentially results in disability, which can have severe consequences such as stigma and poverty.^3^ Leprosy has a long and variable incubation time, ranging from 2 to 20 years, during which it is assumed that transmission can take place.^4^ The risk of developing leprosy is higher in household contacts and neighbours of patients than it is in the general community.^5^ Moet *et al* demonstrated that physical and genetic distance were independently associated with the risk of a contact developing leprosy.^6^ According to the WHO, contact screening should be offered to a person who has been in contact with an untreated leprosy index case for at least 20 hours per week during at least 3 months in the previous year.^4 7 8^ An index case is defined as a person diagnosed with leprosy for the first time.^7^

The WHO has provided multidrug therapy free of charge to all patients with leprosy since 1995.^9^ However, to overcome ongoing transmission in high-endemic areas, innovative measures are needed.^8 10^ In 2008, a large randomised controlled trial in Bangladesh (Chemoprophylaxis for leprosy study, COLEP) demonstrated that a single dose of rifampicin (SDR) given to contacts of newly diagnosed patients with leprosy is effective in reducing the risk of leprosy by 57% (95% CI: 24% to 75%).^11^ Post-exposure prophylaxis with single-dose rifampicin (SDR-PEP) was found to be cost-effective in Bangladesh.^12^ In the Leprosy Post-Exposure Prophylaxis (LPEP) programme, SDR-PEP was implemented in areas representing various health systems across three continents and eight countries, to evaluate the feasibility, effectiveness and impact.^13^ The implementation of SDR-PEP within the routine leprosy control programmes was proven to be safe and generally well accepted. Based on the LPEP programme and a microsimulation leprosy model (SIMCOLEP), SDR-PEP was also found to be cost-effective in India.^14^ The concern that SDR-PEP could lead to increased rifampicin resistance in other diseases, such as tuberculosis (TB), was considered in an expert consultation that concluded that SDR-PEP given to contacts of patients with leprosy, in the absence of symptoms of active TB, poses a negligible risk of generating resistance in *M. tuberculosis* in individuals and in populations.^15^ In 2018, SDR-PEP was included in the WHO ‘Guidelines for the diagnosis, treatment and prevention of leprosy’. Once contact tracing has been established, SDR-PEP can be included into the routines of leprosy control programmes with minimal additional efforts and costs.^7 16^

Skin screening is an important detection strategy for skin-NTDs such as leprosy, and is recommended to be embedded in leprosy programmes.^1 7 17 18^ Screening for multiple skin diseases at once (integrated or common skin screening) is promoted by WHO.^1 8 19 20^ Integration is considered to increase effectiveness and efficiency by minimising costs and expanding intervention coverage.^19 21^ An important obstacle for integrated skin screening is the scarcity of dermatologists in many areas with a high skin NTD endemicity.^22^ In sub-Saharan Africa, the situation is critical, with approximately one dermatologist per 500 000–1 million inhabitants and even larger shortages in Mozambique and Tanzania according to oral field reports from PEP4LEP consortium members.^23 24^ According to the WHO, community health workers and village volunteers can play a role in screening for skin diseases, but improved knowledge, capacity and motivation of health workers and community volunteers is essential.^17 19 25–29^ As both integrated skin screening for NTDs and SDR-PEP against leprosy are promoted by the WHO, additional implementation studies are necessary to establish whether a combined intervention is acceptable, feasible and cost-effective in leprosy endemic areas.^1 4 8 19^

### Objectives

The PEP4LEP project is a collaboration among study consortium members in five countries in sub-Saharan Africa and the European Union (EU) (figure 1). The overall aim of this cluster-randomised implementation trial is to contribute to the interruption of *M. leprae* transmission by identifying the most effective and feasible method of screening people at risk of developing leprosy and by administering post-exposure chemoprophylaxis in Ethiopia, Mozambique and Tanzania. The primary study objectives are to compare the effectiveness and feasibility of a community-based screening and prophylaxis intervention (skin camp) with a health centre-based screening and prophylaxis intervention solely for household contacts of a leprosy patient. The case detection delay will be the primary outcome measure to assess effectiveness. Additional objectives are to assess the cost-effectiveness, acceptability and health workers’ capacity regarding the integrated skin diseases approach and the use of the supportive mobile health (mHealth) tool SkinApp.^30 31^

**Figure 1 F1:**
[figure not shown]
PEP4LEP project organisation chart.

## Methods and analysis

### Study setting

This study will take place in three countries in sub-Saharan Africa: Ethiopia, Mozambique and Tanzania. The three countries differ socioculturally and in the endemicity of NTDs like leprosy (figure 2).^2^ Districts within these countries were purposefully chosen because of endemicity and the focal distribution of reported leprosy cases. In Ethiopia, three endemic districts are located in East Hararghe Zone (Oromiya region): Girawa, Jarso and Midega. In Mozambique, the included districts are located in Nampula province: Meconta, Mogovolas, and Murrupula. The Tanzanian districts are Lindi in Lindi Region and Morogoro and Mvomero in Morogoro Region. The original overall study period was October 2018 until January 2023, with an estimated duration of 2.5–3 years for the inclusion of patients with leprosy and their contacts. A study extension is expected due to the impact of COVID-19.

**Figure 2 F2:**
[figure not shown]
PEP4LEP countries’ leprosy incidence in 2019 according to the WHO (2020).^2^

### Participants and eligibility criteria

Patients with leprosy enrolled in the PEP4LEP study are referred to as ‘index patients’. These patients were derived from the leprosy programme registries, and preferably diagnosed up to 6 months prior to inclusion to prevent recall problems when assessing the delay in case detection.^32^ The inclusion and exclusion criteria for index patients and contacts are summarised in table 1 and are based on the WHO guidelines and the LPEP programme.^4 13^ Following the emergence of the COVID-19 pandemic, a suspicion of a COVID-19 infection was added as contact exclusion criteria for this study, as physical distancing cannot be guarded when performing skin screening.^33–36^ Study participants recovered from COVID-19 can still be included after they have been tested negative and are symptom-free for at least 2 weeks.^33–35^

**Table 1 T1:** PEP4LEP eligibility criteria patients and contacts^4 7 13^

	Index patients	Contacts
Inclusion criteria	Consent to participate in the PEP4LEP project. Diagnosed with leprosy (preferred maximum of 6 months prior to inclusion).^32^ Residence in the PEP4LEP districts for ≥3 months prior to the date of diagnosis. Index patient has started MDT. Community-based skin camp intervention: Patient with leprosy gives permission for the set-up of a skin camp in his/her community (sharing their leprosy diagnosis with their contacts is not needed). Health centre-based household screening intervention: Patient with leprosy with household contacts, and who is willing to inform these contacts about PEP4LEP.	Consent to participate in the PEP4LEP project. Community-based skin camp intervention: Community contact (living in the 20 closest houses to the index-patient) for ≥3 months. Health centre-based household screening intervention: Contact which is a household member of the index patient for ≥3 months, visiting the screening health centre ≤3 months after the index patient was included.
Exclusion criteria	Index patient or parents/legal guardians unable to understand the purpose and risks of participating in the PEP4LEP study.	Contact or parents/legal guardians unable to understand the purpose and risks of participating in the PEP4LEP study. Age <2 years and/or <10 kg of weight.* Pregnancy.* Receiving or having received rifampicin for any reason in the last 2 years. Known allergy to rifampicin. History of liver or renal disorders. Individuals with leprosy and those who have possible signs and/or symptoms of leprosy (eg, leprosy-like skin lesions or nerve manifestations) until their disease status has been clarified.† Individuals with possible signs and/or symptoms of TB (cough for more than 2 weeks or cough in known patients with HIV/AIDS, night sweats, unexplained fever, weight loss) until their disease status has been clarified.‡^113^ Individuals with possible signs and/or symptoms of COVID-19 (self-assessed temperature ≥38°C, respiratory or cold-like symptoms, sudden loss of smell/taste) or possible contact with a patient with COVID-19 in the past 14 days.‡^33–36^

*A voucher will be given for repeated skin screening and SDR-PEP. This can be used in a PEP4LEP affiliated health centre when this person becomes eligible (eg, after giving birth).

†If referral was needed and no leprosy is detected, repeated skin screening and SDR-PEP can be provided in a PEP4LEP affiliated health centre.

‡Skin screening and SDR-PEP can only be provided in a PEP4LEP affiliated health centre after the contact is tested negative for COVID-19/TB (according to national guidelines).^33–36^

MDT, multidrug therapy; SDR-PEP, single-dose rifampicin post-exposure prophylaxis; TB, tuberculosis.

The target population for the feasibility component of this study as well as the other research objectives, consists of various stakeholders, including: (index) patients, household contacts, community contacts, community leaders, health workers, community health volunteers and health policy decision-makers. If applicable, contacts refusing to receive skin screening and/or SDR-PEP, but who are willing to participate in the qualitative component will also be included in the project, contributing to the acceptability component of the study.

The exclusion criterion for these stakeholders is refusal to provide informed consent to participate.

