
### Randomisation

PEP4LEP used randomisation without blinding at the (clustered) health centre level (health centres/posts), ensuring that clusters were similar in size. There are 17 health facilities included in Ethiopia, 22 in Mozambique and 23 in Tanzania. Blinding is not possible because of the varying operational components of the interventions. Cluster randomisation is commonly used when trying to capture the impact of an intervention at community level on both infectiousness and susceptibility.^75^ This method is stated to be feasible logistically, and contamination (eg, information-sharing between participants from both interventions) is unlikely.^75^ Randomisation was performed using the statistical software package R.^76^ Per country, health centres were randomly divided into the community-based intervention or health centre-based intervention.

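### Index patients enter under different inclusion rules in each arm after open cluster allocation, so randomisation does not assure that the delay comparison is like with like

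*Protocol article*

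**What the plan says.** Table 1 (Participants and eligibility criteria) lists criteria that every index patient must meet: consent, a leprosy diagnosis, at least 3 months' residence in a study district, and treatment started. It then adds one condition per arm.

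- Health-centre arm: the index patient must be a "Patient with leprosy with household contacts, and who is willing to inform these contacts about PEP4LEP".
- Community arm: the requirement is "Patient with leprosy gives permission for the set-up of a skin camp in his/her community", and Table 1 adds that "sharing their leprosy diagnosis with their contacts is not needed". Household contacts are not required.

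The Randomisation section states that health centres were allocated within each country and that "Blinding is not possible because of the varying operational components of the interventions". Study setting describes the enrolment period "with an estimated duration of 2.5–3 years for the inclusion of patients with leprosy and their contacts".

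On who supplies the primary outcome, the strengths and limitations box says "only recently diagnosed index patients will be included in this study to establish case detection delay", and the Sample size section sizes the trial on delay in 675 index patients. The Data analysis section compares mean or median delay between the arms and with baseline. It counts cases found by contact screening and by passive case finding, and does not mention the arm-specific conditions.

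**The concern.** Randomising health centres balances their catchment populations in expectation. It does not balance patients who are then filtered by a rule that differs between the arms. A patient who lives alone, or who will not tell the household, can enter in a community cluster but not in a health-centre cluster. A patient who refuses a camp is lost only in a community cluster.

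Both filters could be related to delay. The section on the skin camp intervention says that stigma makes people affected by leprosy reluctant to reveal their status. Such reluctance could plausibly also postpone a first consultation, which is the patient-delay part of the outcome. If so, mean delay among enrolled index patients could differ between arms with no intervention effect. A larger sample would not remove that difference, and no analysis can recover delays that were never collected.

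**Working it through.** **Inputs from the protocol.** Mean delay 24 months, SD 8, target difference 3 months, no design effect (Sample size); two-sided 5% significance (Data analysis). The enrolment targets reproduce: 30 × 3 countries × 3 years = 270; 45 × 3 × 3 = 405; total 675. No power is stated, so 675 cannot be derived from the difference and SD. Nothing below depends on that.

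**Inputs that the protocol does not give.** The share of otherwise eligible patients failing each arm's condition (f), and how much longer their mean delay is than that of patients who pass (d). All values of f and d below are assumptions.

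**Formula.** Let μ be the mean delay of all otherwise eligible patients, the same in both arms when there is no intervention effect. If m is the mean among those who pass, then μ = (1 − f)m + f(m + d) = m + f·d, so m = μ − f·d. Writing H for the health-centre arm and C for the community arm:

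difference (C − H) with no effect = f_H·d_H − f_C·d_C.

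The shift is the net of two filters. If they remove equal shares with equal d, it is 0. With f_H = 10%, f_C = 20% and d = 6 in both, it is 0.6 − 1.2 = −0.6 months. With the shares exchanged it is +0.6.

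**Yardstick.** At 270 and 405 patients, SE = 8 × √(1/270 + 1/405) = 0.629 months. The smallest observed difference reaching p ≤ 0.05 is 1.96 × 0.629 = 1.23 months.

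**Results with no intervention effect**, where f is the net extra share excluded in one arm and d is common to both arms:

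| f | d (months) | shift f·d (months) | false-positive rate |
|---|---|---|---|
| 0% | any | 0 | 5% |
| 5% | 3 | 0.15 | 5.7% |
| 10% | 6 | 0.6 | 15.9% |
| 10% | 12 | 1.2 | 48% |
| 20% | 6 | 1.2 | 48% |
| 20% | 12 | 2.4 | 96.8% |

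The last column uses a two-sided z test with the protocol's assumption of no design effect. If delays are correlated within clusters, the SE is larger and these rates are lower, but the shift in months is unchanged.

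**Who supplies delay data.** The strengths and limitations box, Participants and eligibility criteria, and Sample size all tie delay to enrolled index patients, and so to the arm-specific conditions. The Data analysis section names passively detected cases without stating a condition. If it means every newly diagnosed patient in a cluster, the filters would largely cease to matter for the delay outcome. The text does not settle which is meant.

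**The case against.** The strongest reply is that the bias may be very small. The section on the health-centre intervention says that patients are usually willing to disclose to household members and are more reluctant towards neighbours. It also expects around six household contacts per patient to attend, which suggests that few patients live alone. The community arm has a filter of its own, and patients who fear exposure may refuse a camp too, so the two filters may partly cancel. This stands, and it is why the range starts near zero.

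Three stronger readings are tempting, and the documents do not support them.

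- *The bias runs against the skin camps.* That follows only if the health-centre filter removes more late presenters than the camp-permission filter does. Neither is known.
- *Enrolment as an index patient is the only way a passively detected case can enter the delay data.* Several sections point that way, but the Data analysis section leaves it open.
- *The recency rule contradicts itself.* Table 1 has "Diagnosed with leprosy (preferred maximum of 6 months prior to inclusion", while the strengths and limitations box admits only recently diagnosed patients. The box gives no number of months, so the two are compatible. The preference is the same in both arms, and unequal use of it by unblinded staff would be speculation. Delay ends at diagnosis, so an older diagnosis does not lengthen it by construction. It affects recall, which the questionnaire's local calendar and clinical photographs are there to support.

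One could also say that defining the delay analysis set belongs to the full protocol or analysis plan. That is fair for the analysis set. The inclusion criteria, however, are fixed in this article, and they determine whose delay is collected.

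**Conclusion.** The point holds in a limited form. The inclusion rules for index patients differ by arm and are applied once the openly allocated arm is known, in the group to which most of the protocol ties its main outcome. Comparability of delay is therefore not assured by randomisation. That is not the same as showing that the arms are not comparable.

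Under assumed values the net shift runs from about 0 to 0.15 months, where little needs correcting, up to 0.6–2.4 months, which is 20% to 80% of the 3-month target (0.6/3 and 2.4/3). The documents determine neither size nor direction. The difference in wording between the arms is certain; the resulting bias is only possible. The change is worth making because it is cheap and because delays not collected cannot be recovered later.

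**What to change.** For the delay outcome, use one rule in both arms: every consenting, newly diagnosed patient registered at the cluster's facilities, with the same residence and recency criteria. Interview these patients with the existing questionnaire whether or not they meet the arm-specific condition. Use the household-contact, disclosure and camp-permission conditions only to decide whether contact screening is triggered. Analyse by cluster as randomised, and report by arm how many patients failed each condition. State in the Data analysis section that passively detected cases enter on this common rule. The baseline survey already interviews recently diagnosed patients with the same questionnaire, and no arm condition is stated for it.

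A firm 6-month limit is optional. A sensitivity analysis restricted to diagnoses within 6 months would serve.

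The cost is some rewording and extra delay interviews. If the health-centre arm still enrols 405 patients who meet its condition, a failing share of 5% adds about 21 interviews (405/0.95 − 405) and 20% adds about 101 (405/0.80 − 405). For 270 in the community arm the same shares add about 14 and 68. These shares are assumptions. Patients would still consent knowing their cluster's arm, so selection through consent remains; the change removes only the part created by the rules.

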### Study design

The study is a two-arm, cluster-randomised implementation trial (figure 3). One intervention is community-based, using skin camps to screen approximately 100 community contacts (household members and neighbours) of an index patient with leprosy and to provide them with SDR-PEP when eligible. The second intervention is health centre-based, inviting the household contacts of an index patient to be screened and given SDR-PEP when eligible.

